## Abstract

**Background:**

Parastomal hernia, common after stoma creation, negatively impacts patient quality of life. For patients with a permanent stoma, durable parastomal hernia repair remains a challenge, with few high-quality studies for guidance. An alternative to open retromuscular parastomal hernia repair with retromuscular “keyhole” mesh is the recent Sugarbaker modification. We aim to compare these two techniques in a head-to-head prospective study.

**Methods:**

This is a registry-based randomized controlled trial designed to investigate whether the retromuscular Sugarbaker technique is superior to the retromuscular keyhole technique for parastomal hernia repair. The primary study endpoint is parastomal hernia recurrence at 2 years. Secondary endpoints include hospital length-of-stay, readmission, wound morbidity, mesh-related complications, re-operation, all 30-day morbidity, and patient-reported outcomes, including hernia-related quality of life, stoma-specific quality of life, pain, and decision regret.

**Discussion:**

Based on the post hoc analysis of a recent randomized controlled trial, we hypothesize that the retromuscular Sugarbaker technique will reduce parastomal hernia recurrence by 20% at 2 years compared to the retromuscular keyhole mesh technique. The results of this study may provide evidence-based guidance for surgeons repairing parastomal hernias.

**Trial registration:**

ClinicalTrials.gov NCT03972553. Registered on 3 June 2019

## Administrative information

Note: the numbers in curly brackets in this protocol refer to SPIRIT checklist item numbers. The order of the items has been modified to group similar items (see http://www.equator-network.org/reporting-guidelines/spirit-2013-statement-defining-standard-protocol-items-for-clinical-trials/).

## Introduction

### Background and rationale {6a}

Parastomal hernia after stoma creation is common, occurring in nearly 50% of patients [1, 2]. Problems associated with parastomal hernias—difficulty fitting stoma appliances, parastomal skin breakdown, pain, and bowel obstructions—negatively impact quality of life and push patients to seek repair [3, 4]. Some 800,000 Americans were thought to be living with a stoma in 2003, and an estimated 120,000 stomas are created by surgeons in the USA every year [5]. Parastomal hernia repair, however, remains a challenge. There are no prospective, high-quality studies to guide surgeons and patients in choosing the safest and most durable repair technique. Furthermore, parastomal hernia recurrence rates are high and vary widely despite the repair technique [6].

Parastomal hernias can be repaired using open and minimally invasive approaches. Minimally invasive repairs are typically reserved for smaller parastomal hernias without a concomitant midline hernia, while an open approach is usually preferred in larger, more complex parastomal hernias. Mesh augmentation is used in over 90% of parastomal hernia repairs and has been shown to reduce parastomal hernia recurrences [6, 7]. However, the best mesh configuration to prevent hernia recurrence is unknown. Several centers have evaluated an open retromuscular approach, typically with transversus abdominis release (TAR) and retromuscular mesh placement [8, 9]. Retromuscular mesh reinforcement allows for wide overlap of the midline and parastomal defects in a well-vascularized space and keeps the mesh outside the peritoneal cavity, away from the viscera. Given the high incidence of concomitant midline defects for these patients, this is our most commonly utilized technique.

There are two standard mesh configurations to accommodate the stoma in an open retromuscular approach: keyhole and Sugarbaker. In the keyhole technique, the stoma is pulled through aligned apertures in the mesh and abdominal wall. Using this approach, parastomal hernia recurrence rates at a single institution were 11% at 13 months [8]. In the Sugarbaker technique, the apertures in the abdominal wall are offset and the bowel is placed over the mesh in the retromuscular space [10]. Recently, Pauli et al. found the parastomal hernia recurrence rate to be 4.5% at 10 months using the retromuscular Sugarbaker technique [11]. Additionally, a post hoc analysis of a large randomized controlled trial (RCT) comparing biologic versus synthetic mesh showed a parastomal hernia recurrence rate of 10% at 2 years for the Sugarbaker approach versus 30% for the keyhole approach in 108 patients (*p* = 0.07) (unpublished data). These promising results have prompted the urgent need to perform a well-designed RCT evaluating the outcomes of the two most common parastomal hernia repair approaches at our high-volume center.

### Objectives {7}

We aim to compare clinical and patient-reported outcomes between retromuscular synthetic mesh repairs using the keyhole versus Sugarbaker approach. This will be the first RCT to compare outcomes in open parastomal hernia repairs, giving surgeons critical information to appropriately care for these complex patients.

### Trial design {8}

This is a single-center, parallel-group, superiority, registry-based, prospective RCT. Study data will be captured in the Abdominal Core Health Quality Collaborative (ACHQC) registry and supplemented with Research Electronic Data Capture (REDCap®) when necessary.

## Methods: participants, interventions, and outcomes

### Study setting {9}

This study will be performed at a single site, the Cleveland Clinic Center for Abdominal Core Health, part of the Cleveland Clinic Foundation in Cleveland, Ohio.

### Eligibility criteria {10}

Inclusion criteria:
Adults with a parastomal hernia who are candidates for an open retromuscular parastomal repair with a permanent stoma.

Exclusion criteria:
Two or more stomas preoperativelyInsufficient bowel length for either repair technique as determined by the surgeon intraoperatively.

### Who will take informed consent? {26a}

Informed consent from potential trial participants will be obtained by the study investigator, co-investigators, or research personnel during the preoperative visit.

### Additional consent provisions for collection and use of participant data and biological specimens {26b}

Not applicable, no additional consent provisions needed.

### Interventions

#### Explanation for the choice of comparators {6b}

At our high volume center, keyhole parastomal hernia repair is a popular technique for complex parastomal hernia repairs, but it has a fairly high long-term hernia recurrence rate. In several small single-center series, the open retromuscular Sugarbaker approach has promising results. However, these two techniques have never been compared in a prospective head-to-head trial.

#### Intervention description {11a}

All parastomal hernia repairs will be performed by six fellowship-trained surgeons with experience in abdominal wall reconstruction and gastrointestinal surgery.

Surgical operation:
Patients will be preoperatively marked for a new stoma site by ostomy nurses.All patients will receive preoperative antibiotics per Surgical Care Improvement Project guidelines, in addition to pharmacological and mechanical thromboprophylaxis.All patients will undergo midline laparotomy and adhesiolysis.Stoma re-siting, stoma revision at the same location, or leaving the stoma in situ will be performed at the surgeon’s discretion and documented appropriately.After confirming adequate bowel length for either repair technique, patients will be randomized by study coordinators to the Sugarbaker or keyhole technique using a computer-generated treatment allocation in REDCap®.Bilateral retromuscular dissections will be performed.

For the keyhole mesh group:
If the stoma has been left in situ, the posterior rectus sheath is closed and a lateral or superior slit is made in the mesh to accommodate the bowel. The slit in the mesh is then sewn back together with permanent suture, creating an aperture for the bowel and allowing all elements of the abdominal wall and mesh to align.If the stoma has been taken down, the bowel is brought through a cruciate incision in the posterior rectus sheath or contiguous peritoneum. The posterior rectus sheath is then closed. The bowel is then pulled though a cruciate incision in the mesh, just large enough to accommodate it, and finally through the stoma opening in the anterior fascia. The aperture in the mesh may be tightened with permanent suture at the surgeon’s discretion. Apertures in the posterior rectus sheath, mesh, and anterior fascia are all aligned.

For the Sugarbaker group:
If the stoma has been left in situ, a lateral slit is made in the peritoneum and a V-Y peritoneal advancement flap created to “lateralize” the bowel through the peritoneum.If the stoma has been taken down, a cruciate incision is made in the lateral peritoneum to accommodate the bowel.The posterior rectus sheath is then closed. The bowel then traverses the retromuscular space—over the mesh—to the stoma aperture, which is medial to the cruciate incision in the peritoneum. The length of retromuscular traverse is left to the surgeon’s discretion and bowel length, but in general, it is encouraged to be as long as possible. The bowel is then brought through the anterior fascia medially so the apertures in the abdominal wall are offset.A medium-weight, appropriately sized polypropylene mesh is deployed in the retromuscular space for both repair types.Closed-suction drains are placed in the retromuscular space. The retromuscular space is irrigated, and the anterior fascia and skin are closed.If the stoma was taken down, it is re-matured.

#### Criteria for discontinuing or modifying allocated interventions {11b}

The primary endpoint will be analyzed via intention-to-treat. When patients experience complications requiring re-operation and conversion of the stoma to the alternative treatment arm, all subsequent adverse events will be attributed to the randomized repair technique.

#### Strategies to improve adherence to interventions {11c}

The research coordinator will not randomize participants until the surgeon confirms adequate bowel length for a Sugarbaker repair intraoperatively.

#### Relevant concomitant care permitted or prohibited during the trial {11d}

Concomitant care is not restricted during this trial. Postoperative care will follow our standard enhanced recovery after surgery protocol [12].

#### Provisions for post-trial care {30}

We have no provisions for ancillary or post-trial care, or for compensation to those who suffer harm from trial participation.

### Outcomes {12}

Primary endpoint:
Two-year parastomal hernia recurrence assessed by:
Physical examPatient-reported recurrence using the colostomy impact score [13]Computed tomography (CT)

Secondary endpoints:
Hospital length-of-stayReadmissionRe-operationMesh-related complicationsAll 30-day morbidityWound morbidity
Surgical site infections (SSI)Surgical site occurrences (SSO)Surgical site occurrences requiring procedural intervention (SSOPI)
Reoperation
Wound debridementMesh excision
PartialCompleteStoma revisionPatient-reported outcomes at 30 days (± 15 days), 1 year (± 4 months), and 2 years (± 6 months).
Short-form Patient-Reported Outcomes Measure Information System (PROMIS) Pain Intensity Scale [14]Hernia-Related Quality-of-Life Survey (HerQLes) score [15]Colostomy Impact Score [13]Decision Regret Scale [16]

### Participant timeline {13}

See participant timeline (Fig. 1).

**Fig. 1 Fig1:**
[figure not shown]
Participant timeline

### Sample size {14}

Based on the post hoc analysis of a large RCT, we predict that the retromuscular Sugarbaker technique will be superior to the keyhole mesh approach and reduce 2-year parastomal hernia recurrence by 20%. With an *α* of 0.05 and power of 80%, we calculated a necessary sample size of 118 patients—59 in each arm to demonstrate this 20% absolute reduction in 2-year parastomal hernia recurrence. Assuming a 20% rate of patients lost to follow-up, an enrollment goal of 142 patients was defined.

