### Implementation {16c}

Participants will be enrolled by the surgeon during the preoperative consultation. The intraoperative allocation sequence will be generated by the research coordinator in REDCap®.

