### Methods in analysis to handle protocol non-adherence and any statistical methods to handle missing data {20c}

The primary endpoint will be analyzed via intention-to-treat. When patients experience complications requiring reoperation and conversion of the stoma to the alternative treatment arm, all subsequent adverse events will be attributed to the randomized repair technique. Sensitivity analysis will be performed using a per-protocol methodology.

Missing data is anticipated to reflect a pattern of missing at random. Multiple imputation will be used to impute missing data at baseline only and provide the missing at random assumption holds. Multiple imputation of follow-up measures will not be performed. If non-random missing data patterns are observed, alternate methods, such as pattern mixture models, will be considered.

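### The enrolment goal of 142 adds 20% to 118 instead of dividing by 0.80, so it preserves the required 118 only up to 16.9% loss, not the stated 20%

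*Protocol article*

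**What the plan says.** All the figures in question stand in one paragraph of the protocol article, Sample size {14}. On the requirement it says: "With an *α* of 0.05 and power of 80%, we calculated a necessary sample size of 118 patients", split as "59 in each arm to demonstrate this 20% absolute reduction in 2-year parastomal hernia recurrence". On attrition it says: "Assuming a 20% rate of patients lost to follow-up, an enrollment goal of 142 patients was defined".

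The paragraph names a post hoc analysis of an earlier randomised trial as its basis. Background and rationale {6a} gives that analysis's result: a "parastomal hernia recurrence rate of 10% at 2 years for the Sugarbaker approach versus 30% for the keyhole approach".

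The missing-data section {20c} bears on what happens to patients who are lost: "Multiple imputation of follow-up measures will not be performed".

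**The concern.** The paragraph makes three statements: 118 patients are needed, 20% will be lost, and 142 will be enrolled. They cannot all hold. Adding 20% to the requirement is not the same as allowing for a 20% loss, because the loss is taken from the larger, enrolled number. The added margin is therefore always too small, and the error always runs towards under-enrolment.

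What is at stake is the accuracy of the sentence that justifies the sample size for the primary endpoint. A reader would conclude that the trial keeps 80% power with one patient in five lost, and on the plan's own assumptions it falls slightly short of that. The plan has no slack to absorb the difference, because 59 per arm is the minimum under the formula that appears to have been used. Follow-up outcomes will not be multiply imputed, so a patient with no 2-year assessment adds nothing to the binary primary outcome.

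**Working it through.** **Inputs**

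- Significance level 0.05, power 80%, 20-point absolute reduction, equal arms: Sample size {14}. That section does not say whether the test is one- or two-sided; two-sided is assumed.
- Recurrence of 30% (keyhole) and 10% (Sugarbaker) at 2 years: Background and rationale {6a}.
- Loss 20%, goal 142: Sample size {14}.

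**Step 1. Reproduce the requirement of 118.** The unpooled normal approximation for two proportions is

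n per arm = (z₀.₉₇₅ + z₀.₈₀)² × [p₁(1 − p₁) + p₂(1 − p₂)] / (p₁ − p₂)²

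= (1.96 + 0.8416)² × (0.21 + 0.09) / 0.04 = 58.87, so 59 per arm and 118 in total.

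This matches the plan. The pooled-variance formula would give 62 per arm (124 in total), so the unpooled formula is the natural reading of how 118 was obtained.

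**Step 2. Reproduce the goal of 142.** 118 × (1 + 0.20) = 141.6, so 142. This also matches, and it shows how the goal was reached.

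**Step 3. Apply the stated loss to 142.** 142 × (1 − 0.20) = 113.6, about 114 patients or 57 per arm. The shortfall against 118 is about 4.

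**Step 4. Correct inflation.** 118 / (1 − 0.20) = 147.5, so 148 (74 per arm). Check: 148 × 0.80 = 118.4. The difference from the stated goal is 148 − 142 = 6.

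**Step 5. Loss that 142 can absorb.** (142 − 118) / 142 = 24/142 = 16.9%.

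**Step 6. Power at the reduced number**, for 30% versus 10% and a two-sided 5% level. The unpooled formula is power = Φ(√(n × 0.04 / 0.30) − 1.96).

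- n = 59: √7.867 = 2.805, and Φ(0.845) = 80.1%.
- n = 57: √7.600 = 2.757, and Φ(0.797) = 78.7%.

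| Method | 59 per arm | 57 per arm | Fall |
|---|---|---|---|
| Unpooled (reproduces the plan) | 80.1% | 78.7% | 1.4 points |
| Pooled | 78.2% | 76.8% | 1.4 points |
| Chi-squared test, exact enumeration | 80.5% | 78.9% | 1.6 points |

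If 113 patients remain (57 keyhole, 56 Sugarbaker), exact enumeration gives 77.9%, a fall of 2.6 points from 80.5%. At the unrounded 56.8 per arm, the unpooled formula gives 78.6%, a fall of 1.5 points.

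Steps 2 to 5 use only 118, 20% and 142. They do not depend on the test, its sidedness or the recurrence rates. Only step 6 does.

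**The case against.** The strongest counter-argument concerns size. The error costs about 4 evaluable patients and about 1.5 points of power. It biases nothing and does not touch the analysis. The 20% loss is itself an assumption, and the 30% and 10% rates come from an unpublished post hoc comparison with p = 0.07, so uncertainty in the inputs far exceeds the effect of this slip. All of that stands, and it makes this a minor correction. It does not make the sentence right: nothing elsewhere in the article rescues 142, and the fix is free.

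Three stronger readings are tempting, and the document does not support them.

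- A reader might infer that power drops from 80% to about 77%. That figure comes from the pooled formula, which already gives only 78.2% at the full 59 per arm. More than half of that gap is due to the choice of formula. The inflation error accounts for 1.4 points under either formula.
- A reader might infer that patients excluded during surgery for bowel length use up places among the 142. Implementation {16c} does say: "Participants will be enrolled by the surgeon during the preoperative consultation". Randomisation follows later, once the surgeon has confirmed bowel length. But the article nowhere says that patients excluded in this way count towards the goal, and it gives no rate for such exclusions. Since 142 is built directly from 59 per arm, reading it as randomised patients is at least as natural. This is a point of wording, not a further shortfall.
- A reader might fault the sample-size section for omitting the two recurrence rates. They are given in the background section, for the analysis that the sample-size section names as its basis, so repeating them is a matter of presentation.

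**Conclusion.** The enrolment goal is wrong as written. A 20% loss from 142 leaves about 114 evaluable patients, not the 118 described as necessary, and 142 protects that number only up to 16.9% loss. This conclusion rests on the paragraph's own three figures and on reading the loss rate as a share of the patients entered, which is its natural meaning.

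The effect on power is minor: about 78.7% at 20% loss by the formula that reproduces the plan's 59 per arm. That estimate assumes 30% versus 10% recurrence, a two-sided 5% level and roughly equal loss in the two arms. It does not suggest that the trial is materially underpowered or that its result would be unsound.

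**What to change.** Correct the sentence in Sample size {14}. Either of two forms would do:

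- Keep 142 and state what it delivers: 118 evaluable patients, and so 80% power, if up to about 17% are lost; about 79% power if 20% are lost. This adds no patients and needs one sentence.
- State 148 randomised patients (74 per arm), which keeps both the 20% allowance and the 80% power. This adds six patients.

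The first is the more practical. Recruitment {15} expects about 50 repairs a year over 3 years, about 150 in all, so 148 would need almost every repair to be randomised.

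As an optional clarification in the same sentence, say whether the 142 counts randomised patients. This costs nothing.

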### Recruitment {15}

The Cleveland Clinic Center for Abdominal Core Health is a high-volume hernia center, performing approximately 50 parastomal hernia repairs per year. We expect to complete enrollment within 3 years.

## Assignment of interventions: allocation

### Sequence generation {16a}

Intraoperative computer-generated treatment allocation in REDCap® will randomize participants to keyhole versus Sugarbaker technique.

### Concealment mechanism {16b}

Not applicable, the patients are randomized intraoperatively after the surgeon confirms adequate bowel length for either repair technique.

### Implementation {16c}

Participants will be enrolled by the surgeon during the preoperative consultation. The intraoperative allocation sequence will be generated by the research coordinator in REDCap®.

## Assignment of interventions: blinding

### Who will be blinded {17a}

Study participants, those collecting patient-reported outcomes, and 2-year CT scan assessors will be blinded to repair technique.

### Procedure for unblinding if needed {17b}

Participants may be unblinded to their repair technique if they experience complications requiring re-operation.

## Data collection and management

### Plans for assessment and collection of outcomes {18a}

Patient characteristics and operative details will be captured in the ACHQC database, per our practice standard. Patient-reported quality of life at baseline will be collected with the standard ACHQC questionnaire, which includes the short-form PROMIS Pain Intensity Scale [14] and HerQLes, validated for assessing quality-of-life related to abdominal wall function [15]. Preoperative stoma-related quality of life will also be assessed using the validated Colostomy Impact Score questionnaire [13].

Postoperative clinical outcomes, including hospital length-of-stay, readmission, re-operation, mesh-related complications, and wound morbidity, will be captured in the ACHQC registry and in REDCap®. Wound morbidity, including SSIs, SSOs, and SSOPIs, will be reported using standard definitions [17].

Postoperative visits at 30 days, 1 year, and 2 years postoperatively (our practice standard-of-care) will include a physical exam and collection of patient-reported outcomes. Patient-reported outcomes will be assessed using the standard postoperative ACHQC questionnaire, which includes the short-form PROMIS Pain Intensity Scale and HerQLes. Additional postoperative questionnaires will capture Colostomy Impact Scores and Decision Regret Scales, validated for measuring regret after health care decisions [16].

Parastomal hernia recurrence will be evaluated by physical exam, patient-reported outcomes (colostomy impact score), and radiography. Physical exam will identify a parastomal hernia if there is bulging in the vicinity of the stoma. Colostomy impact score will identify a recurrence if patients respond “Yes, I have a small bulge (under 10 cm)” or “Yes, I have a larger bulge (over 10 cm).” CT recurrence will be defined as protrusion of a separate and distinct segment of bowel or other intra-abdominal contents within the musculofascial aperture. Three surgeons, blinded to the operative surgeon and repair technique, will evaluate radiographic recurrences, and at least two of three assessors must agree on radiographic hernia recurrence for it to be documented as such.

Parastomal hernia recurrence reporting will likely be influenced by missing data and by the many possible permutations of physical exam, patient-reported outcomes, and radiographic findings, so a consensus definition of hernia recurrence was established using all possible scenarios [18]. Two additional definitions of hernia recurrence will be included for sensitivity analyses, performed to evaluate hernia recurrence over its ranges by defining the best- and worst-case scenarios.

Best-case scenario: hernia recurrence calculated on the most conservative definition of recurrence (maximum specificity), using the algorithm to report the lowest recurrence rate.Worst-case scenario: hernia recurrence calculated on the most inclusive definition of recurrence (maximum sensitivity), using the algorithm to report the highest recurrence rate.

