## Statistical methods

### Statistical methods for primary and secondary outcomes {20a}

Analyses will be done under the normality assumption, if appropriate. Patient characteristics will be summarized overall and by randomized group, and differences will be described as standardized effects. All analyses, using the intent-to-treat population, will be performed with SAS and R software (version 9.4, Cary, NC; version 4.0.0, Vienna, Austria, respectively). Tests will be considered significant at a 5% level.

The primary study endpoint is 2-year composite hernia recurrence rate as a binary outcome (yes or no). Unadjusted and adjusted logistic regression will compare recurrence rates between the two repair techniques at 2 years. The adjusted model will include pre-specified covariates related to baseline disease severity: patient BMI, recurrent parastomal hernia, stoma disposition (stoma re-matured at a new site versus not), and type of stoma. Results, obtained using g-computation, will be presented as relative and absolute risk differences with a 95% confidence interval. Unbalanced follow-up times will be accounted for by using rate ratio and rate difference. As a sensitivity analysis, we will assess the treatment effect on time to hernia recurrence using a Cox proportional hazard model. Results will be presented by hazard ratio and 95% confidence interval, while adjusting for the pre-specified covariates.

The secondary endpoints are not dependent on the primary endpoint. The secondary endpoints are hospital length-of-stay, readmission, wound morbidity (SSI, SSO, or SSOPI), re-operation (stoma necrosis, mesh-related complication, mucocutaneous stoma disruption, and hernia recurrence requiring reoperation), and patient-reported outcomes, including PROMIS scores, HerQLes scores, opioid consumption at 30 days, stoma-relatedquality-of-life, and decision regret scores. Comparisons of categorical endpoints will be performed using chi-squared tests or Fisher’s exact test. Comparisons of continuous endpoints will be performed using two-sample*t*-tests or Wilcoxon rank-sum tests.

Additional analysis, such as mediation analysis, will be performed if the Data Safety and Monitoring Board (DSMB) or the investigators suspect potential dependent endpoints (for example, SSI and 2-year recurrence).

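### The stoma quality-of-life score is compared by an unadjusted two-sample test, although stoma type and the preoperative score are already collected and could be adjusted for at no cost

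*Protocol article*

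**What the plan says.** All references are to the protocol article.

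- **Eligibility criteria {10}** admits "Adults with a parastomal hernia who are candidates for an open retromuscular parastomal repair with a permanent stoma". The exclusions are two or more stomas and insufficient bowel length. Neither list restricts the kind of stoma.
- **Plans for assessment and collection of outcomes {18a}** names the instrument at baseline: "Preoperative stoma-related quality of life will also be assessed using the validated Colostomy Impact Score questionnaire". For follow-up it says: "Additional postoperative questionnaires will capture Colostomy Impact Scores and Decision Regret Scales". Outcomes {12} sets these at 30 days, 1 year and 2 years.
- **Statistical methods for primary and secondary outcomes {20a}** adjusts the primary recurrence model for covariates tied to baseline severity, among them "stoma disposition (stoma re-matured at a new site versus not), and type of stoma". The same covariates enter the Cox sensitivity analysis.
- The same section lists stoma-related quality of life among the secondary endpoints and fixes the test: "Comparisons of continuous endpoints will be performed using two-sample*t*-tests or Wilcoxon rank-sum tests". No covariate is attached to it.
- **Methods for additional analyses {20b}** rules out further subgroup analyses.

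**The concern.** The plan treats stoma type in two ways. For recurrence it is considered prognostic enough to be a pre-specified covariate. For the one endpoint that measures how patients live with the stoma, it does not enter the analysis. The preoperative value of the same score, usually the natural covariate for a follow-up score, is not used in the comparison either.

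If mean scores differ between stoma types, or if follow-up scores track preoperative scores, an unadjusted comparison carries that variation in its standard error. The interval for the treatment difference is then wider than the collected data require. The stake is precision on a named secondary endpoint. Type I error and bias are not at issue.

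**Working it through.** **1. What the plan's own figure covers.** Sample size {14} gives 59 per arm, α 0.05 and 80% power for a 20-point absolute reduction. The Background gives 30% against 10%. With unpooled variance and a two-sided test:

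n = (1.960 + 0.842)² × (0.3×0.7 + 0.1×0.9) / 0.2² = 7.85 × 0.30 / 0.04 = 58.9, so 59 per arm.

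The figure reproduces. It was derived for recurrence. The article states no effect, SD or power for the Colostomy Impact Score and no stoma mix, so everything below is an assumed range.

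**2. Benchmark effect.** With 59 per arm, the difference detectable with 80% power after adjustment for stoma type is 2.802 × √(2/59) = 0.516 within-type SD.

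**3. Effect of leaving stoma type out.** Let q be the share of patients with a non-colostomy stoma and d the mean shift in score between the two groups, in within-type SDs. The unadjusted variance is inflated by

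V = 1 + q(1 − q)d²,

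and power becomes Φ(2.802/√V − 1.960).

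| q (assumed) | d (assumed) | V | Power of unadjusted test |
|---|---|---|---|
| any | 0 | 1.000 | 80.0% |
| 0.10 | 0.25 | 1.006 | 79.8% |
| 0.25 | 0.25 | 1.012 | 79.5% |
| 0.25 | 0.5 | 1.047 | 78.2% |
| 0.50 | 0.5 | 1.062 | 77.6% |
| 0.25 | 1.0 | 1.188 | 72.9% |
| 0.40 | 1.0 | 1.240 | 71% |
| 0.50 | 1.0 | 1.250 | 70.7% |

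Because the benchmark is set at 80% power, these values depend on V and not on n. They are the same at 71 per arm (142/2).

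**4. Chance imbalance is not a further loss.** At q = 0.4 the between-arm difference in stoma mix has SD √(2×0.4×0.6/59) = 0.090. With d = 1 this moves the estimate by about 0.09 SD. Its variance is 0.48/59 = 0.0081. Adding it to 2/59 = 0.0339 gives 0.0420, which is 1.24 × 2/59. It is therefore the same quantity as V at q = 0.4 and d = 1, and must not be counted twice.

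**5. Baseline score.** If preoperative and follow-up scores correlate at ρ within stoma type, adjustment multiplies the residual variance by about 1 − ρ². The article gives no ρ, so I put no figure on this gain.

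**6. What adjustment cannot do.** If the score responded only half as strongly in non-colostomy patients, the average effect would shrink by the factor 1 − q/2. At q = 0.25 that is 0.875, and power is Φ(2.802×0.875 − 1.960) = 68.8%. A stoma-type term does not restore this.

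**The case against.** Much of the case on the other side stands.

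- **The planned test is sound.** Randomisation balances stoma type in expectation, so the unadjusted comparison is valid and unbiased. Adjustment is a gain in efficiency, not a repair.
- **The size is assumed.** The covariate is not broken down into categories, so the article shows that stoma type varies but not what share is non-colostomy. With no shift between types, the loss from ignoring stoma type is zero.
- **It is one secondary endpoint among many.** The trial is sized on recurrence only, and an analysis plan not shown may already refine this comparison. The point survives only because the article itself states the test. The Discussion's remark that satisfaction may matter more than recurrence is tied to the Decision Regret Scale, so it adds no weight here.

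A reader might infer more: that an instrument named for colostomy is mis-scaled in other patients, so that a null result would reflect the questionnaire. The article does not support this. It cites a source for the score's validation but gives neither the validation population nor the scoring, and it describes only the two bulge responses. The name alone is not evidence of how the score behaves with other stomas.

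A reader might also want the colostomy-only estimate treated as the proper reading. That too lacks support, and it does not help. Suppose the score is half as responsive in 20%, 40% or 60% of patients, with 57 per arm (142 × 0.8 / 2). The pooled test then has power Φ(2.802(1 − q/2) − 1.960) = 71%, 61% and 50%. The colostomy-only test has Φ(2.802√(1 − q) − 1.960) = 71%, 58% and 43%. Its interval is 1/√0.6 = 1.29 times as wide as the pooled one at 40% and 1/√0.4 = 1.58 times at 60%. It would also work as a subgroup analysis, which section {20b} rules out.

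**Conclusion.** The point holds as a question of efficiency. The plan fixes an unadjusted test for the Colostomy Impact Score, while it collects stoma type, treats it as prognostic in the primary model, and measures the same score before surgery. The cost of omitting stoma type lies between nothing and about 2 points of power for shifts up to 0.5 SD with a non-colostomy share up to 25%. It reaches about 9 points for a 1 SD shift with a share of 40% to 50%. These figures rest on an assumed mix, an assumed shift and a benchmark of 80% power after adjustment. The further gain from the baseline score cannot be sized from the article.

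Nothing in the article shows that the score is invalid in non-colostomy patients or that the planned comparison is biased. This is a low-cost improvement to a secondary analysis.

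**What to change.** In Statistical methods {20a}, take the Colostomy Impact Score out of the general two-sample rule. Analyse the follow-up score at each visit by linear regression on randomised arm, adjusted for type of stoma (coded as in the primary model) and the preoperative score. Report the adjusted mean difference with its 95% confidence interval.

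The cost is one sentence of plan wording and one regression that spends a few degrees of freedom. Both covariates are already collected, and section {20c} already provides for multiple imputation of missing baseline data. No new patients or visits are needed, and the recurrence endpoint, including its use of the score's bulge item, is unchanged. The description of the score as validated can stay as it is, and no colostomy-only analysis is needed.
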